### Blinding

The participant, hospital staff and project coordinator are blinded to the allocation until the participant is discharged upon which the randomisation occurs. Thus, the hospital treatment and discharge should not be affected by the enrolment of the participant. After discharge, when the patient is randomised, the participant, the project coordinator, the geriatric nurse, the community nurse, and the primary care physician will no longer be blinded. The project coordinator is not involved with the patients after the patient has been discharged, except if the patient is readmitted and invited to participate in the project again.

Prior to data analysis, all IDs will be linked to a new scrambled ID, and the old ID is hidden as will all identifying data (social security number, address). This will be done by a third party to ensure that the data analyst will not know which group is the intervention and which is the control group. All data analysis will thus be done blinded.

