**Fig. 1 Fig1:**
[figure not shown]
Study design

Eligible patients are informed about the project (orally and in writing) and invited to join. If they accept, they sign an informed consent. They are randomised on the day of discharge to either the intervention or control group. In the case of a planned discharge during the weekend, the participants are randomised on Friday. Participants randomised to the control group receive a usual discharge, while participants in the intervention group receive a usual discharge as well as a coordinated follow-up visit, which is planned to take place 2–5 working days after the day of discharge.

For all participants (control and intervention), administrative and clinical data will be collected from hospital records and the hospital administrative system, e.g. hospital discharge diagnoses, LOS, medication, medical history, Charlson Comorbidity Index [29] and Barthel Activities of Daily Living (ADL) score.

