***Secondary outcomes***		
Outcome 3	Mortality (1 year)	Proportion of participants deceased within one year
Outcome 4 Outcome 5	Time to Readmission Days alive out of hospital	Proportional hazard model of readmission with a total duration of 1 year and median time to readmission estimated by Kaplan–Meier method Days spent alive out of the hospital within 30 and 90 days from discharge
Outcome 6	Clinical assessments/POCT measurements and their association to decision making	Regression analysis of the association between conducting a clinical measurement (e.g. Saturation, temperature, Sodium, CRP) or POCT analysis and the risk of readmission
Outcome 7	Costs associated with the intervention	Analysis of the costs associated with the intervention and potential savings from the result of the intervention
Outcome 8	User perspectives among involved participants and professionals	Analysis of questionnaires and focus group interviews with involved groups, including participants, community nurses, geriatric nurses, geriatric physician, and primary care physician

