### Data collection

Data will be collected at several points. The data will all be saved and stored in a secure database (REDCap). All personnel involved will be trained data collection.

Before the participant is invited to join the study, data is gathered on eligibility (i.e. diagnosed moderate to severe dementia, residence location to identify citizens of Odense Municipality, and type, use of home care, terminal diseases and presence of delirium).

Before discharge, data is gathered from the participants’ electronic medical records regarding discharge diagnoses, LOS, medication, medical history and Barthel ADL score [39]. A Clinical Frailty Score [40] is assessed by a geriatric nurse.

All data collected during the follow-up visit is registered in our database, including the data gathered in the FS-III survey, vital status and POCT results. The vital parameters and POCT results will be used to understand their influence on the clinical decision making.

The data collected during the follow-up visit will be filled directly into pre-defined fields in REDCap and will help ensure that all the necessary data is collected.

All participants, controls and interventions will receive a questionnaire, which is a modified version of a previously validated questionnaire [41]. At the time of randomisation, both groups will be asked about their satisfaction with the treatment, care and hospitalisation in general, as well as if they feel safe being discharged. A follow-up questionnaire will be administered to both groups by telephone. Data will be transferred to REDCap manually. The questionnaires will be administered by project coordinators who are not involved in the clinical care of the patients.

Data on death and readmissions will be collected from electronic medical records for 1 year after the allocation date for each participant.

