### Statistical analyses

Statistical analyses will be carried out STATA Version 17 (StataCORP LLC, Texas, USA).

We will exclude participants with single-item missing data relevant to the analysis and will not perform imputations. An intention-to-treat analysis will be employed to maintain the integrity of our results. A per-protocol analysis will also be performed to complement the primary intention-to-treat analysis. While the intention-to-treat analysis preserves the advantages of randomisation and reflects real-world implementation challenges, the per-protocol analysis may help assess the true effect of receiving the intervention as intended. Given the negligible planning costs and absence of adverse effects, the intervention may still be considered clinically relevant even if statistical significance is only observed in the per-protocol population.

Characteristics will be reported with numbers, percentages and means with standard deviations or medians with interquartile range, as appropriate. Differences will be calculated using appropriate tests. Appropriate regression analyses will be conducted according to advice from a research statistician. Threshold for significance will be *P* < 0.05.

Readmission and mortality will be calculated and compared as relative risks. We will conduct an interim analysis after 1 year to adjust the time length of the study and to assure that one group does not have a significantly higher mortality rate or readmission rate than the other, which are the stopping criteria. The outcomes examined in the interim analysis will be 30-day mortality and 30-day readmission rate. The interim analysis will be conducted on data masked by a third party to ensure blinding, and the data will not be unblinded unless there is a significant difference in mortality, which is the only stopping criteria. The interim analysis will be conducted after 13 months have passed, i.e. January 2024.

The financial costs analyses will be conducted under supervision of a health economist, [name]. We will analyse our data including time spent by the health professionals and estimate intervention cost per participant, which will be compared to an estimated daily cost of admission and the estimated avoided readmission days.

Qualitative analysis will be conducted to assess user perspectives. This will be conducted as a separate parallel study by [name] [name].

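### The claim that all analysis is blinded cannot hold for the POCT outcome and is very unlikely to hold for the per-protocol analysis; it should be limited to the intention-to-treat comparisons and backed by a staged data release

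*Protocol article*

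**What the plan says.** Under Blinding, the article explains that before analysis a third party replaces each ID with a scrambled one and hides identifying data. The stated purpose is that "the data analyst will not know which group is the intervention and which is the control group", and the conclusion drawn is "All data analysis will thus be done blinded". No exception is made for any analysis.

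Other sections describe what the analyst will work with:

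- **Recruitment and enrolment:** "Participants randomised to the control group receive a usual discharge". The home visit is added in the intervention group only.
- **Data collection:** "All data collected during the follow-up visit is registered in our database, including the data gathered in the FS-III survey". Vital status and POCT results from the visit are stored there too.
- **Table 2, Outcome 6:** "Regression analysis of the association between conducting a clinical measurement (e.g. Saturation, temperature, Sodium, CRP) or POCT analysis and the risk of readmission".
- **Statistical analyses:** a per-protocol analysis accompanies the intention-to-treat analysis, and "the intervention may still be considered clinically relevant even if statistical significance is only observed in the per-protocol population". The same section plans a costing that includes staff time, overseen by a health economist.
- **Analyses of primary and secondary outcomes:** participants who had the intervention at an earlier enrolment are analysed separately.

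**The concern.** Scrambling an ID hides who a person is. It does not hide a block of variables that is filled for one group and empty for the other. Several planned analyses draw on such variables, yet the article presents masking as a property of every analysis.

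A reader will take the sentence to mean that modelling decisions were made without knowledge of the arms. That matters most where decisions remain: which covariates enter the adjusted and secondary models, and who counts as per-protocol. The second has weight here because the article allows a per-protocol result to support clinical relevance when the intention-to-treat result does not. If the analyst has seen visit fields beside the group code before those decisions are made, the protection that the sentence promises is absent.

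**Working it through.** The claim rests on no figure, so there is nothing to recompute. The check takes each planned analysis and asks whether it needs a field that only one arm can have.

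**Step 1: which fields exist in one arm only.** Table 1 schedules vital parameters and the FS-III problem areas both at discharge and at the home visit, and POCT measurements at the home visit only. The discharge values exist in both arms and reveal nothing. The visit values and all POCT results can exist only for visited intervention participants.

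**Step 2: what one such field does to the code.** Suppose the file holds a group code A/B. A single completed visit record under A identifies A as the intervention. Intervention participants with no visit record look like controls one by one, but that does not restore the masking of the code.

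**Step 3: the planned analyses in turn.**

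- *30-day and 90-day readmission, mortality, time to readmission, days alive out of hospital:* these need the group code, baseline data and outcomes. No visit field is required, so they can be masked. The interim analysis, on 30-day mortality and readmission, is of this kind.
- *Adjustment for participants already readmitted at recruitment:* this needs a baseline flag that says nothing about current allocation. It can be masked.
- *Outcome 6:* this needs to know whether a measurement was made at the visit. It cannot be masked.
- *Per-protocol:* this needs receipt of the visit. Even if the third party supplied only an in/out flag, exclusions for a missed visit can arise in one arm only, and a lopsided count would point to that arm. This is a strong inference rather than a certainty, since the article does not define the population and a few exclusions might go unnoticed.
- *Costs (Outcome 7):* staff time and intervention cost per participant belong to the intervention arm, while admission days exist in both. The arm is revealed to whoever opens the staff-time fields, and the article does not say that this is the outcome analyst.
- *Prior-intervention analyses:* the label refers to an earlier enrolment, not the current one. It breaks the code only if a person's two records can be linked after scrambling, so that the earlier record's code can be read beside the label. The article does not say whether they can.

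**Step 4: is anything stated that keeps these apart?** The only means given are new IDs and the hiding of identifying data. The article does not say that visit fields are left out of the file used for the arm comparisons, nor in what order the analyses are run.

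**Result.** The word *all* fails for Outcome 6, very probably fails for the per-protocol analysis, and may fail for two more analyses. If everything is supplied as one file, the intention-to-treat comparisons lose their masking too.

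**What a per-protocol choice looks like.** The Aim gives the visit window as 2–5 days, while Recruitment and enrolment and the Intervention section give 2–5 working days. These passages must be reconciled, and until they are, who was visited as intended depends on a choice that should be made without the arms in view.

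**The case against.** The strongest reply is that the sentence is loose wording. Masking is meant for the comparison between arms, and the main comparisons can be masked. Outcome 6 compares no arms, so masking has no function there. The cost work may be done by other people. Data-release order, covariate lists and model specification normally belong in an analysis plan or data-management plan, and such a document may exist.

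Most of this stands, and it rules out three stronger readings that a reader might infer:

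- *That four analyses reveal the arm with certainty.* Only Outcome 6 clearly does. The per-protocol analysis very probably does; the cost and prior-intervention analyses do so only under conditions on which the article is silent.
- *That blinded analysis is impossible in this design, or that the primary result is compromised.* The intention-to-treat comparisons need no visit field, and the unadjusted 30-day relative risk leaves no covariate choice to influence.
- *That open covariates and models are themselves the fault.* The article does say "Appropriate regression analyses will be conducted according to advice from a research statistician" and lists risk factors only as examples. It also names intention-to-treat, relative risks, the Cox and Kaplan–Meier methods and adjustment for readmitted participants, and an unseen analysis plan may fix the rest. Masking to A/B would in any case stop choices made by direction, not choices made by significance; only a model fixed in advance stops both.

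The per-protocol sentence is likewise a separate question of interpretation, and would remain one under perfect masking. It is relevant here only because it raises the value of fixing that population before the arms can be seen.

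What the reply does not remove is that the published statement covers every analysis, and the article's own plan contradicts it. An unseen plan could make the practice sound, but would not make that statement true.

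**Conclusion.** The point holds in limited form, as a minor one. Scrambled IDs cannot deliver blinding for Outcome 6 and are very unlikely to do so for the per-protocol analysis. They protect the intention-to-treat comparisons only if visit-level fields are kept out of the file on which those comparisons are run, which the article does not state.

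The exposure is to the adjusted and secondary models and to the choice of per-protocol population. Its size cannot be derived from the document, and no bias is asserted. The conclusion assumes that visit fields are filled for visited intervention participants only, as the article describes, and that one analyst may hold both the group code and those fields, which the article neither states nor excludes.

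**What to change.** Release the data in two steps, using the third party already engaged.

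1. **Masked file:** group code, baseline data (including the flag for participants readmitted at recruitment) and outcomes. It holds no visit, POCT, visit FS-III, staff-time or prior-allocation fields. The intention-to-treat analyses are completed on this file and the per-protocol definition is fixed in writing.
2. **Visit-level file:** released only after step 1, for the per-protocol, Outcome 6, cost and prior-intervention analyses, which are then reported as not blinded.

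Replace the sentence under Blinding with: *The intention-to-treat between-group analyses will be done blinded.*

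The cost is one extra data transfer and one reworded sentence. Sample size, outcomes and trial conduct are unchanged. If a combined file has already been released, the report should say which analyses were completed before visit fields were seen.

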### Study outcome

The study outcomes are listed in the table below. Overall, we have several main focus areas:

The primary aim is to examine whether an early follow-up visit carried out simultaneously by a geriatric nurse and a community nurse can remedy a recently discharged participant’s health problems related to the hospital admission and reduce readmission. As such, the main outcome is 30 days acute readmissions. A readmission is defined as any hospital visit with a LOS of 12 h or longer, as this is in accordance with the definition of acute readmission by the Danish National Health Services [38]. Other aims include the use of in-home clinical assessment and use of POCT to understand their value in the clinical assessment, and their feasibility in an in-home setting. In addition, user perspectives on the home visit are a central outcome covering participants, community nurses, the geriatric nurses and the geriatrician. Other outcomes are the most common post-discharge health-related problems that arise or become apparent in the first days after discharge. Finally, health economic analysis will be carried out (Table 2).

**Table 2 Tab2:** Project outcomes

Outcome		Outcome measure
***Primary outcomes***		
Outcome 1	Readmission (30 days)	Acute readmission to a Danish hospital within 30 days from hospital discharge
Outcome 2	Readmission (90 days)	Acute readmission to a Danish hospital within 90 days from hospital discharge

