### Data analyses

#### Sample power and statistical power

Based on our recent finding of a 28% reduction in readmissions following geriatric follow-up to discharged geriatric patients [42], and using a 2-proportions with 2-sample equality power test, a current readmission rate of 19% (control group), and an expected 28% reduction by the intervention, the readmission rate in the intervention group is (19 − (19 × 0.28)) 13.68%. If the proportions of group A, *pA*, is (100 − 19 =) 81 and proportion of group B,* pB*, is (100 − 13.68 =) 86.32,* α* = 0.05,* β* = 0.80 and* К* = 1, the sample size should include 763 in each group, and 1526 patients totally [43]. The total finally becomes 1832 after accounting for an expected dropout rate of 20%. The Department of Geriatric Medicine at Odense University Hospital is expected to discharge about 1500–1800 patients in 2022–2023 alone, which makes it feasible to include enough participants to reach statistically significant results in 2 years. We had originally calculated a shorter time period for the study, however, due to COVID and nurse shortage, the number of beds has been reduced. We have included statistics for all inclusion and exclusion criteria in our model for estimation of the time required for the study.

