### Analyses of primary and secondary outcomes

The primary outcome is 30-day acute readmission. We will use relative risks to compare the readmission rates in the two groups. Relative risk for other readmission time frames will also be calculated to improve comparisons with other studies.

Competing risk of death will be considered in our analyses, as it can skew the results. Partially due to this, days out of hospital will also be calculated as it is less affected by the competing risk of death than a binary readmission outcome.

We will also calculate the relative risks for 30-day mortality.

A proportional hazard model will be used to explain the time to readmission. This will be done using the Cox regression model. Moreover, median time to readmission will be estimated by the Kaplan–Meier method.

We will include relevant patient characteristics that are known risk factors in our statistical analyses, e.g. multimorbidity, polypharmacy and length of stay.

Throughout the analyses, we will adjust for participants that were already readmitted at the time of recruitment. Separate analyses will be done for patients that already received the intervention, as there may be a residual effect of the intervention.

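### Table 2 makes 30-day and 90-day readmission both primary while the text names 30-day alone, leaving two routes to success at P<0.05

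*Protocol article*

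**What the plan says.** The protocol article describes the primary outcome in several places.

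- **Table 2 (Study outcome).** Under a plural heading for primary outcomes, Outcome 1 is "Acute readmission to a Danish hospital within 30 days from hospital discharge" and Outcome 2 is "Acute readmission to a Danish hospital within 90 days from hospital discharge". Secondary outcomes begin at Outcome 3.
- **Study outcome, text above the table.** One outcome only: "the main outcome is 30 days acute readmissions".
- **Analyses of primary and secondary outcomes.** One outcome only: "The primary outcome is 30-day acute readmission". Other windows get a supporting role: "Relative risk for other readmission time frames will also be calculated to improve comparisons with other studies".
- **Aim.** Mentions readmission at 30 days and no other window.
- **Sample power and statistical power.** One comparison, 19% against 13.68%, at alpha 0.05 and 80% power, giving 763 per group. No 90-day rate or effect appears.
- **Statistical analyses.** One rule for all tests: "Threshold for significance will be *P* < 0.05". No order of testing, division of alpha or both-must-succeed rule is given.

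**The concern.** The document gives 90-day readmission two incompatible roles. In Table 2 it is primary, on equal terms with 30-day readmission. In the analysis section it is one of the additional windows reported for comparison with other studies. The text introduces Table 2 as the list of study outcomes, so a reader could fairly treat the table as definitive.

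This is a superiority trial, and its conclusion turns on which outcome is primary. If both are primary and each is tested at 0.05, a result on either one can be presented as success, and the stated 5% error rate does not hold. Even if no one intends that, the conflict lets the headline be settled after both results are seen. Masking the group labels during analysis does not prevent this, because the analyst can still see which of the two outcomes is significant.

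**Working it through.** **1. The plan's own sample size is a single test at full alpha.**

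Inputs from the sample size section: p1 = 0.19, p2 = 0.19 − 0.19 × 0.28 = 0.1368, alpha 0.05 (taken as two-sided), power 0.80, equal groups.

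n = [1.96 × √(2 p̄(1 − p̄)) + 0.8416 × √(p1(1 − p1) + p2(1 − p2))]² / (p1 − p2)², with p̄ = 0.1634.

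This gives 758 per group (755 with unpooled variance), against 763 stated. Power at 763 per group is 80.3%. A one-sided test would need only 597, so 0.05 is two-sided. The full 5% is spent on one outcome and nothing is reserved for a second.

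**2. Correlation between the two tests.**

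Every patient readmitted within 30 days is also readmitted within 90 days, so the indicators are nested. Their covariance is p30(1 − p90), and the correlation is

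r = √[ p30(1 − p90) / (p90(1 − p30)) ].

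p30 = 0.19 is the plan's readmission rate. The article does not attach a window to it; I take it as 30 days because it is used to size the 30-day comparison. The article gives no 90-day rate, so p90 is an assumption. Example at p90 = 0.30: r = √(0.19 × 0.70 / (0.30 × 0.81)) = √(0.133 / 0.243) = 0.74.

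**3. Chance of at least one significant result when the intervention affects neither outcome.**

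P(either) = 1 − P(|Z1| ≤ 1.96 and |Z2| ≤ 1.96), with (Z1, Z2) bivariate normal with correlation r.

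| Assumed 90-day rate | r | P(at least one significant) |
|---|---|---|
| 25% | 0.84 | 7.5% |
| 30% | 0.74 | 8.15% |
| 35% | 0.66 | 8.5% |
| 40% | 0.59 | 8.8% |
| 45% | 0.54 | 9.0% |
| 50% | 0.48 | 9.1% |

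Independent tests would give 1 − 0.95² = 9.75%; nesting keeps the figure below that. A simulation of 200,000 null trials with 763 per arm gave 7.5%, 8.6% and 8.8% at 90-day rates of 25%, 35% and 45%, in line with the table.

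**4. What each repair does.**

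- 30-day as sole primary, 90-day secondary: error on the primary question 5%, sample size unchanged.
- Fixed order, 30-day then 90-day: overall error 5%, sample size unchanged.
- Equal split, 0.025 each: 917 per group (1,834 before dropout) for 80% power on 30-day readmission, or power of 71.6% at 763 per group.

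**The case against.** The best defence is that the text points one way and only the table heading disagrees. The aim, the outcome text, the sample size and the analysis section all fit a single 30-day primary outcome, and the sentence on other time frames treats them as supportive. On that reading the error rate is 5% and the fault is a wrong table label. Nothing in the article says that either outcome alone would suffice, so the inflated figure needs two conditions: the table overrides the text, and either outcome may win. A rule for multiple testing could also sit in a statistical analysis plan that is not shown.

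Part of this stands. The 8.1% to 8.8% is conditional, and it depends on an assumed 90-day rate and on reading 19% as a 30-day figure. The absence of a testing rule is not a separate fault. The contradiction remains, however. The article assigns 90-day readmission to the primary outcomes in one place and excludes it in another, and does not say which prevails. Condensing a protocol explains missing detail, not an explicit table row that conflicts with the text. An analysis plan built on this protocol would inherit the conflict. That most of the text favours 30 days is a reason to correct the table.

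**Conclusion.** The plan is wrong as written: it defines its primary outcome in two incompatible ways. If the text governs, the false-positive rate is the intended 5%. If Table 2 governs and either outcome can carry the trial, it is about 8.1% to 8.8% for assumed 90-day readmission rates of 30% to 40%, and 7.5% to 9.1% over 25% to 50%. These figures assume a 30-day rate of 19%, two-sided tests at 0.05 and no effect on either outcome. The contradiction itself depends on none of these assumptions. The stated sample size supports only the single-primary reading.

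**What to change.** Move Outcome 2 (90-day readmission) from the primary to the secondary block of Table 2, leaving 30-day acute readmission as the only primary outcome. This brings the table into line with the aim, the outcome text, the sample size and the analysis section.

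If the sponsor wants both to remain primary, state a fixed order: test 30-day readmission at 0.05, and test 90-day at 0.05 only if the first is significant. An equal alpha split is the poorer choice, given the loss of power shown above.

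The edit is one table row, or one sentence for the fixed order, and the power for 30-day readmission is untouched. The price is that 90-day readmission alone can no longer make the trial positive. Timing also matters: recruitment began in November 2022, an interim look at 30-day readmission was set for January 2024, and the article appeared in July 2025. The correction should therefore be dated and justified, shown to precede any unmasked comparison of the groups, and checked against the trial registration.
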